# Effects of the Chinese herbal formula San-Huang Gu-Ben Zhi-Ke treatment on stable chronic obstructive pulmonary disease: study protocol of a randomized, double-blind, placebo-controlled trial

**DOI:** 10.1186/s13063-019-3729-1

**Published:** 2019-11-27

**Keywords:** Chronic obstructive pulmonary disease, Traditional Chinese medicine, Chinese herbal formula San-Huang Gu-Ben Zhi-Ke, Clinical trials, Clinical protocols

## Abstract

**Background:**

Due to the large number of patients, high mortality rate as well as high social costs and economic burden, chronic obstructive pulmonary disease (COPD) has become one of the most important health problems around the world, which has attracted people’s attention. Currently, Chinese herbs have been widely used as alternative medicine (CAM) for COPD patients. The Chinese herbal formula San-Huang Gu-Ben Zhi-Ke (SHGBZK) has shown good clinical efficacy in COPD in preclinical studies. Animal experiments have shown that it has mucosal immune barrier function and can maintain airway wall integrity, reduce inflammatory cell infiltration, promote inflammatory damage repair, and relieve narrow airway conditions.

**Methods/design:**

This study is a randomized, double-blind, placebo-controlled trial. A total of 100 patients with stable COPD diagnosed with deficiency of lung qi and spleen qi will be recruited and randomly assigned to one of two treatment groups: SHGBZK treatment, *N* = 50; placebo treatment, N = 50. The two groups will receive basic treatment for COPD according to the 2017 GOLD Guidelines for Chronic Obstructive Pulmonary Disease. Patients will stick to the treatment they used to take as much as possible, and will be given present general treatment when acute exacerbation of COPD occurs during the study. Both groups will receive a 24-week intervention and patient status will be assessed at 24 weeks and then 28 weeks after treatment. After the 24-week treatment, patients will be followed up for another 28 weeks. Outcome measures, including the frequency and duration of acute exacerbation, lung function, traditional Chinese medicine symptom score, exercise capacity, and quality of life will be assessed.

**Discussion:**

It is hypothesized that SHGBZK will have beneficial effects in reducing the frequency and duration of acute exacerbations, improving the exercise capacity function of patients with stable COPD diagnosed with a deficiencies in lung qi and spleen qi. This study may establish a new treatment method for COPD patients, differentiating it from other drugs in clinical use used for similar clinical indications.

**Trial registration:**

Chinese Clinical Trial Registry, ChiCTR1800016349. Registered on 26 May 2018.

## Background

Chronic obstructive pulmonary disease (COPD) is characterized by persistent and limited airflow, which can be progressively aggravated. The repeated acute exacerbation of COPD (AECOPD) can lead to a variety of complications that lead to the disease worsening [1]. Reducing AECOPD is a major goal of COPD management and an important indicator for evaluating treatments. According to statistics [2], the global incidence of COPD is about 10% of the population. It is expected that COPD will have the third highest fatality rate in the world [3] and its economic burden will rank fifth in the world by 2020. In China, the prevalence of COPD in people over 40 years old is 8.2% [4], the number of deaths due to COPD exceeds one million each year, and the number of disabled people over five million. In addition to pulmonary symptoms, studies have shown that the most common complications of COPD patients are cardiovascular disease, diabetes, asthma, and anemia [5]. Most patients have one or two complications, which increase the social and economic burden. And most patients have mental anxiety symptoms [6], which seriously affect their working ability and quality of life [7]. As COPD can be prevented, effective preventive measures will help to delay the recurrence and progressive aggravation of the disease.

Current treatments for COPD include inhaled corticosteroids and bronchodilators [8]. Although effective at alleviating symptoms, these treatment methods do not alter disease progression. There is a pressing need to find better treatments [9] for improving clinical symptoms, lowering lung function decline, reducing mortality, and shortening hospitalization time. Traditional Chinese medicine (TCM) has a great advantage in reducing the risk for severe exacerbation, improving lung function, positively impacting quality of life, and improving exercise capacity in stabilized patients with COPD, which can supplement the deficiency of modern medical treatment [10].

SHGBZK Chinese medicine is a Chinese herbal formula developed by [name], a great doctor of Chinese medicine with more than 50 years of clinical experience. Preliminary clinical data demonstrated that it has good clinical efficacy in COPD and no obvious side effects [11]. Animal experiments have shown that it has mucosal immune barrier function and can maintain airway wall integrity, reduce inflammatory cell infiltration, promote inflammatory damage repair, and relieve airway narrow conditions [12]. This study aims to evaluate the efficacy and safety of SHGBZK Chinese medicine for further research into developing a new, safe, and effective method for the treatment of stable COPD.

### Study objectives

This study will evaluate the safety and efficacy of the Chinese herbal formula SHGBZK as a treatment for patients with stable COPD diagnosed with deficiency of lung qi and spleen qi.

### Design and setting

One-hundred patients with stable COPD are randomly assigned to two treatment groups (SHGBZK Chinese medicine treatment, *N* = 50; placebo treatment, *N* = 50). The two groups will receive basic treatment for COPD according to the 2017 GOLD Guidelines for Chronic Obstructive Pulmonary Disease. Both groups will receive a 24-week intervention and patient status is assessed at 24 weeks and then 28 weeks after treatment.

### Main outcome measures

The primary outcome is frequency of AECOPD. The secondary outcomes are duration of AECOPD, TCM symptom score, lung function, COPD Assessment Test (CAT) score, Modified Medical Research Council (MMRC) grade, BODE (Body mass index, airflow Obstruction, Dyspnea and Exercise capacity) score, and 6-min walking distance .

## Methods

### Study design

We will conduct a randomized, double-blind, placebo-controlled trial. A flowchart of the study protocol is shown in Fig. 1.

**Fig. 1 Fig1:**
[figure not shown]
Flow chart of the study, a randomized, double-blind, placebo-controlled trial. A total of 100 patients will be recruited and randomly assigned to one of the two treatments group, with 50 in each group. One-hundred COPD patients will be randomly assigned to two treatment groups (SHGBZK treatment, *N* = 50; placebo treatment, N = 50). The two groups will receive basic treatment for COPD according to the 2017 GOLD Guidelines for Chronic Obstructive Pulmonary Disease. Patients will stick to the treatment they used to take as much as possible and will be given the trial treatment when AECOPD occurs during the study. Both groups will receive a 24-week intervention, and patient status will be assessed at 24 weeks and then 28 weeks after treatment. The outcome measures, including the frequency and duration of acute exacerbation, lung function, TCM symptom score, exercise capacity, and quality of life, will be assessed. Patients need to take medication as directed by the doctor. The use of glucocorticoids, antibiotics, mucolytic agents, and antitussive agents is prohibited during the study except if AECOPD occurs, and oral or external Chinese medicine preparations with the effect of tonifying the spleen and lung are prohibited during the trial period

### Ethics and recruitment

All patients will sign informed consent before inclusion. The study has been approved by the Ethics Research Committees of the China–Japanese Friendship Hospital with identifier 2018–57-K41–1. Any revisions of the study protocol will be submitted to the ethics committee.

COPD patients will be recruited from either the out-patient department or open recruitment. Recruitment began in November 2018 and will continue until a sample of 100 patients are enrolled.

### Inclusion criteria

The inclusion criteria are:
The diagnostic criteria in the “Guidelines for the diagnosis and treatment of chronic obstructive pulmonary disease” (2013 revision) [13]Patients with stable symptoms such as cough, sputum production, or breathlessness for 4 weeks with no AECOPDThe risk assessment of AECOPD is high (in the past year, two or more AECOPD occurrences or hospitalized at least once due to AECOPD)TCM syndrome pattern of lung qi and spleen qi deficiency as per the Guidelines for TCM Diagnosis and Treatment of Chronic Obstructive Pulmonary Disease (2011 edition) [14]Aged between 40 and 80 yearsWith informed signed consent and voluntary participation in the study

### Exclusion criteria

Exclusion criteria include:
Confirmed diagnosis of pneumonia and/or moderate to severe AECOPD in the past 4 weeksAccepted pneumonectomy in the past or lung volume reduction surgery in the 12 months before screeningAccepted long-term oxygen therapy (time > 15 h/day) or mechanical aeratorPatients with a history of asthma, active tuberculosis, lung cancer, bronchiectasis, pulmonary embolism, pulmonary heart disease, interstitial lung disease, or other active diseasesPatients with lower extremity activity limitation and unable to complete the 6-minute walk testPatients diagnosed with serious hypertension, diabetes, tumors, or primary heart, liver, kidney, or blood system diseaseScr exceeds the upper limit of the reference value by 1.5 times, or AST/ALT ratio ≥ 2 times the upper limit of the reference valuePatients with congenital or acquired immunodeficiency diseasePatients who are known or suspected of a history of alcohol or drug abusePatients with confusion, dementia, or any kind of mental illnessPregnant or breast-feeding womenAllergic to the used medicineFrequent use of oral glucocorticosteroidsPatients enrolled in other clinical trials during the previous 3 monthsAnyone researchers believe should not participate in the clinical trial

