##### Safety

Routine blood, urine, and stool tests, liver and kidney function tests, and an electrocardiogram will be performed. Adverse events will be recorded at any time during the treatment period and follow-up period.

Adverse events will be recorded and graded in detail throughout the study, such as possible side effects (no side effects of the herbs have been reported so far). If a severe adverse event occurs, participants will be provided with every necessary treatment, and the event must be reported to the leader of the trial, ethics committees, sponsors, and China Food and Drug Administration (CFDA) within 24 h.

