### Screening and run-in, baseline, treatment periods, and endpoint

Adverse events, physical examination, AECOPD situation and MMRC, CAT, and TCM symptom scores will be recorded at baseline (week 0) and every 4 weeks during the study period. The 6-min walking distance and BODE will be recorded at weeks 0, 4, 12, 24, 32, and 52. Lung function will be observed at weeks 0, 24, and 52. Safety will be measured at weeks 0, 12, and 24, not including adverse events and the physical examination. The schedule of assessments and interventions is depicted in Fig. 2.

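### The only laboratory liver exclusion is worded as an AST/ALT ratio, which does not measure how far either enzyme is raised

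*Protocol article*

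**What the plan says.** In the protocol article, one item under Exclusion criteria holds both laboratory limits. Its liver half excludes on "AST/ALT ratio ≥ 2 times the upper limit of the reference" value. Its kidney half excludes when serum creatinine is above its upper limit by 1.5 times.

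No other section restates the liver limit, gives a separate limit for AST or ALT, or gives a reference limit for the ratio. The same list also excludes patients diagnosed with primary liver disease, and anyone the researchers judge unsuitable. Neither of these carries an enzyme value.

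Safety is part of the stated aim: "This study will evaluate the safety and efficacy of the Chinese herbal formula SHGBZK" (Study objectives). Under Safety, "liver and kidney function tests, and an electrocardiogram will be performed". The section on screening, baseline and treatment periods gives the timing: "Safety will be measured at weeks 0, 12, and 24".

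**The concern.** A liver-enzyme exclusion is there to keep out patients whose enzymes are already raised beyond a set level. A ratio cannot do that, because a rise shared by both enzymes cancels. The criterion also compares a ratio, which has no unit, with an upper reference limit that the article does not define for a ratio.

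Three things are at stake.

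- **Eligibility.** Staff who apply the text literally and staff who read it as a limit on each enzyme would enrol different patients.
- **Exposure.** The one numeric liver safeguard before 24 weeks of treatment does not respond to the abnormality it is meant to screen for.
- **Interpretation.** Liver tests are a laboratory safety measure. Grossly raised starting values make it harder to judge an individual patient's week-12 or week-24 result, and harder to read the within-group comparisons of pretreatment with posttreatment values that the Statistical analysis section plans.

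**Working it through.** The article gives no figure to reproduce here, so the check applies the criterion as a rule to illustrative pairs of values.

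**Inputs from the article.** The quantity is AST/ALT, the multiplier is 2, and the comparator is an upper reference limit that is not specified further.

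**Assumptions not in the article.** ULN = 40 U/L for each enzyme. If the ratio has its own upper limit, call it L and try L = 1.0, 1.15, 1.5 and 2.0. The cut-offs 2 × L are then 2.0, 2.3, 3.0 and 4.0.

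**Why the ratio fails.** Write AST = a × ULN and ALT = b × ULN, with the same ULN for both. Then AST/ALT = a/b. Multiplying both enzymes by any common factor leaves the ratio unchanged.

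**Reading 1: the limit belongs to the ratio. Exclude if AST/ALT ≥ 2 × L.**

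| AST | ALT | Multiples of ULN | AST/ALT | Excluded at |
|---|---|---|---|---|
| 200 | 200 | 5 and 5 | 1.00 | none of the four |
| 400 | 400 | 10 and 10 | 1.00 | none |
| 200 | 320 | 5 and 8 | 0.625 | none |
| 240 | 200 | 6 and 5 | 1.20 | none |
| 36 | 12 | both normal | 3.00 | L = 1.0, 1.15, 1.5 |
| 38 | 10 | both normal | 3.80 | L = 1.0, 1.15, 1.5 |
| 35 | 14 | both normal | 2.50 | L = 1.0, 1.15 |
| 39 | 8 | both normal | 4.88 | all four |

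A rise confined to AST could still trip the rule. A joint rise, or one larger in ALT, does not.

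**Reading 2: the limit is the enzyme limit in U/L.** The ratio would have to reach 2 × 40 = 80. No pair in the table comes near that, so the criterion excludes practically nobody.

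**Contrast only, not a proposed threshold.** If the same multiplier were applied to either enzyme against its own limit, the cut-off would be 2 × 40 = 80 U/L. The first four rows would then be excluded and the last four would not, which reverses the classification at every L for the raised pairs.

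**Creatinine, the other half of the item.** With an assumed ULN of 100 µmol/L, the natural reading gives 1.5 × 100 = 150 µmol/L. A strictly literal reading gives 100 + 1.5 × 100 = 250 µmol/L.

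**The case against.** The best defence is that this is a slip of wording. A multiple of an upper reference limit is the form used for a single analyte, and the creatinine half of the same item uses it that way. The intended text was very likely a limit on the enzymes. The article condenses a fuller protocol that is not shown, and nothing indicates that anyone computed a ratio at screening. This is persuasive about intent. It does not rescue the text: the criterion is stated, not left out, and it is wrong as stated.

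Several stronger readings are tempting, and the article does not support them.

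- *Patients with grossly raised enzymes pass screening.* They pass this one criterion. The exclusions for diagnosed liver disease and at the investigator's discretion may still catch them, the second without any prior diagnosis. Whether any such patient was enrolled is unknown.
- *Later abnormal values cannot be attributed to treatment.* The trial is randomised, double-blind and placebo-controlled, with week-0 values for each patient, so a between-group safety comparison remains valid. Only individual attribution and within-group change become harder to interpret.
- *Patients with normal enzymes are being lost, and this hampers recruitment.* That half depends on a ratio limit the article does not give. AST 36 with ALT 12 only just meets the cut-off at L = 1.5 and is not excluded at L = 2.0. The Discussion links recruitment difficulty to strict inclusion criteria, not to this item.
- *The creatinine limit may really be 2.5 times ULN.* That reading is strained beside the liver half of the item. Plain wording would still help, but this is minor.

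**Conclusion.** The point holds as an error in a stated eligibility criterion, and it should be fixed. Under either literal reading, and over assumed ratio limits from 1.0 to 2.0, the criterion does not catch a patient whose AST and ALT rise together, even at 5 or 10 times an assumed ULN of 40 U/L. That conclusion does not depend on the particular ULN, because the common factor cancels. The possible exclusion of patients with two normal enzymes is conditional: it needs the limit to be that of the ratio, and for AST 36 with ALT 12 it needs that limit to be no higher than 1.5.

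The number of patients affected cannot be derived from the article. The primary outcome, sample size and error rates are untouched, and so is the validity of the randomised comparison. For that reason this is a should-fix correction and not a threat to the trial's main result.

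**What to change.** - The sponsor should remove the word *ratio*, or otherwise reconcile the criterion with the enzyme limit that was intended and has actually been applied at screening. The criterion should be expressed on the enzyme values against their own reference limits. The sponsor, not this review, should confirm the multiplier and how the two enzymes are combined.
- In the same amendment, state the creatinine limit plainly as a multiple of its ULN (minor).
- Submit the change to the ethics committee, as the Ethics and recruitment section requires for any revision.
- Recruitment began in November 2018, so check the week-0 liver and kidney values of patients already enrolled and list any whose eligibility changes under the reconciled wording.

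**Cost.** A one-line amendment and a re-check of results already collected. No new test is needed. Eligibility may change for a few candidates in either direction.

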### Withdrawal, dropout, and discontinuation

Participants are free to withdraw at any time during the trial. Participants who wish to withdraw will be offered the option to cease trial medication but continue attending scheduled visits for outcome measurement. Participants who withdraw will be followed to investigate the reason for withdrawal. Participants may be advised to discontinue the treatment if there is a product-related adverse event of a serious nature or if the participant was not compliant with the study requirements. Discontinuers will not be replaced by new participants. Intention-to-treat analysis will be performed on missing data from discontinuers with the last observation carried forward method.

### Sample size

A total of 100 patients will be enrolled in this study with 50 in each group. The frequency of AECOPD is the primary outcome. According to previous studies [15, 16], the exacerbation frequency increased 1.17 times each year when receiving conventional medicine, 0.97 times each year when receiving TCM, and 0.68 times each year when receiving both conventional medicine and TCM. Assume that promotional value is achieved only when the exacerbation frequency decreases at least once for each patient every 6 months. The standard deviation (SD) value is 1.25 times per year, the two-sided α is 0. 05, and β is 0. 10. Based on the formula:
$$ \left(\frac{2{\left({\mu}_{\alpha }+{\mu}_{\beta}\right)}^2{\sigma}^2}{\delta^2}\right) $$of the comparison between the means of the two samples, the sample size in each group is 40. Considering a 20% dropout rate over the course of the study, 50 patients will be enrolled in each group and the total sample size will be 100.

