### Intervention measures

The two groups will receive basic treatment for COPD according to the 2017 GOLD Guidelines for Chronic Obstructive Pulmonary Disease. Patients will stick to the treatment they used to take as much as possible and will be given the trial treatment when AECOPD occurs during the study. Patients in the experimental group will take SHGBZK, while the control group will take SHGBZK placebo. The TCM granules are compound preparations of Chinese herbs; its main components are shown in Table 1 . Each bag of SHGBZK granules (batch number 180606) contains 3 g. The components of the TCM granules are produced and packed by An Hui Ji Ren Pharmaceutical Co. Ltd according to Good Manufacturing Practice (approval number AH20160363), Anhui, PR China. The test results of drug quality were consistent with the required quality standards. Each type of granule will be given orally, four bags each time, three times a day for 24 weeks.

**Table 1 Tab1:** Main components of the traditional Chinese medicine treatment

Chinese name	Latin name	Amount (g)
Chinese herbal formula San-Huang Gu-Ben Zhi-Ke		
Huang Qi	*Astragalus propinquus*	15
Huang Jing	*Polygonatum sibiricum*	12
Chen Pi	*Pericarpium citri reticulatae*	10
Bai Bu	*Stemona japonica*	10
Wu Wei Zi	*Schisandra chinensis*	8
Chi Shao	*Paeonia lactiflora* Pall	10
Huang Qin	*Scutellaria baicalensis* Georgi	8

Patients need to take the medication as directed by the doctor. The use of glucocorticoids, antibiotics, mucolytic agents, and antitussive agents is prohibited during the study except if AECOPD occurs, and oral or external Chinese medicine preparations with the effect of tonifying the spleen and lung are prohibited during the trial period. Patients will be given a daily diary to record their trial medication compliance as well as use of any other therapies and occurrence of adverse events. Patients will be asked to return their medication bags monthly during the treatment period to enable the counting of left-over capsules as well as part of participant adherence monitoring.

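### The 40 per group does not follow from the sample-size inputs, and the target difference is not reconciled with the exacerbation rates quoted beside it

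*Protocol article*

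**What the plan says.** The Sample size section of the Protocol article prints the two-means formula, n per group = 2(u_alpha + u_beta)² sigma² / delta², and gives every input in words.

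- Target difference: "promotional value is achieved only when the exacerbation frequency decreases at least once for each patient every 6 months".
- Variability: "The standard deviation (SD) value is 1.25 times per year".
- Error rates: "the two-sided α is 0. 05, and β is 0. 10".
- Result: "the sample size in each group is 40", raised to 50 for 20% dropout.

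The same paragraph cites rates from previous studies: "the exacerbation frequency increased 1.17 times each year when receiving conventional medicine", 0.97 per year on TCM alone, and "0.68 times each year when receiving both conventional medicine and TCM". Intervention measures states that "The two groups will receive basic treatment for COPD according to the 2017 GOLD Guidelines", so the trial compares TCM plus background treatment with background treatment plus placebo. The Discussion says that the minimum sample size was adopted because recruitment is difficult. It names lung function as the outcome for which the sample is too small.

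**The concern.** Inputs, formula and result are all printed, so a reader should be able to get 40 from them. Two things stand in the way. First, the target is per 6 months and the SD is per year, and no conversion is shown. Second, the target looks very large beside the quoted rates: at 1.17 per year a patient has on average 0.585 events in 6 months, fewer than the one event that is to be prevented.

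Frequency of exacerbation is the primary outcome. A reader will take the 90% power at face value, since the Discussion flags only lung function. If the true difference is close to the one quoted from earlier studies, a non-significant result is about as likely as a significant one, and it could be misread as evidence that the formula does not work.

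**Working it through.** **Inputs** (Sample size section): two-sided alpha 0.05, z = 1.960; beta 0.10, z = 1.2816; SD 1.25 per year; 20% dropout; quoted rates 1.17 and 0.68 per year.

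**Reproducing the stated n.** The formula reduces to

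2 × (1.960 + 1.2816)² × 1.25² / delta² = 32.84 / delta².

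| Reading of the target | delta | SD | n per group |
|---|---|---|---|
| Time units ignored, or 1 per year | 1 | 1.25 | 32.84 → 33 |
| 1 per 6 months, put in the SD's unit | 2 per year | 1.25 | 32.84/4 = 8.2 → 9 |
| Half-year unit, SD scaled by √2 (variance proportional to time) | 1 | 0.88 | 16.4 → 17 |

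None gives 40. Solving for 40 gives delta = √(32.84/40) = 0.906 per year, a value that the plan does not state. The dropout step is right: 40/0.8 = 50.

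Two routes come near 40, and both depart from the text. One is 33 × 1.2 = 39.6, which would count dropout twice. The other is delta 1 at 95% power, which gives 41 but contradicts beta 0.10.

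**Effect of the mismatch on power.** With 40 per group and delta 1 per year, power = Φ(1/(1.25√(2/40)) − 1.960) = Φ(3.578 − 1.960) = 94.7%. The arithmetic error is therefore conservative for the target as stated.

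**Target against the quoted rates.** One per 6 months is 2 per year, against 1.17 per year on conventional medicine. At that rate, abolishing every exacerbation would remove only 1.17 per year. Read as 1 per year, the target is 1/1.17 = 85% of that rate.

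**Power at the quoted add-on difference.** Both arms receive background treatment, so the matching contrast is 1.17 − 0.68 = 0.49 per year.

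- Printed method, 40 per group: Φ(0.49/0.2795 − 1.960) = Φ(1.753 − 1.960) = 42%.
- Printed method, 50 per group: Φ(0.49/0.25 − 1.960) = Φ(0) = 50%.
- n for 90% power: 32.84/0.49² = 136.8 → 137 evaluable per group.

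**Count model as a check** (one year per patient). Matching a negative binomial to mean 1.17 and SD 1.25 gives dispersion k = (1.5625 − 1.17)/1.17² = 0.287. The log rate ratio is ln(0.68/1.17) = −0.543, with per-patient variance term (1/1.17 + k) + (1/0.68 + k) = 2.899.

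- 40 per group: Φ(0.543/√(2.899/40) − 1.960) = 52%.
- 50 per group: 62%.
- n for 90% power: 104 per group.

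A Poisson model would give 61% and 71%, but it contradicts the stated SD, since the variance of 1.5625 exceeds 1.17.

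**The case against.** The strongest reply has four parts.

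- *The mismatch does not weaken the trial.* A reader might infer that because 40 is wrong, power is low. The figures do not support that: 40 exceeds every n that the stated target yields (33, 17, 9). Power is low only at a difference smaller than the stated target. This part stands, and the two defects must be kept apart.
- *The plan declares no control rate.* The 1.17 per year is attributed to previous studies, in unclear wording, and is never adopted as the assumption for the placebo arm. Inclusion criteria require two or more exacerbations or a hospitalization in the past year, so the trial's own rate could be higher. A reader might call the target impossible; that holds only if 1.17 applies here. This stands. A higher rate would not rescue the calculation, however, because delta 2 per year still gives 9.
- *Powering for a worthwhile difference is legitimate.* The target is worded as a threshold of value and not as the expected effect. Failing to power for a smaller historical difference is not in itself an arithmetic error. This also stands, but a threshold still needs one time unit, must yield the n that is reported, and should be explained when it exceeds the only rates quoted.
- *The Discussion already concedes a minimal sample.* That sentence is general, but the consequence it draws concerns lung function only. It does not disclose the power for the primary outcome.

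The text also does not say whether 1.17 and 0.68 come from one randomized comparison, or which patients the SD describes. The power figures at 0.49 per year depend on both.

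**Conclusion.** The sample-size statement is wrong as written. The difference and the SD are in different units, and the printed formula gives 33, 17 or 9, never 40. This rests on the plan's own figures alone.

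Separately, the target is not reconciled with the quoted rates. It is 2 per year against 1.17 per year, or an 85% reduction if read as 1 per year. At the quoted add-on difference of 0.49 per year, power is about 42% to 50% with 40 to 50 evaluable per group by the printed method, and about 52% to 62% with the matched negative binomial. These figures assume that the quoted rates and SD carry over to this trial's higher-risk patients and that each patient contributes about one year.

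The documents do not show that the arithmetic slip caused low power, or that the target is unattainable in this population. Nor do they support 0.91 per year as the intended target: that value comes only from solving backwards from 40.

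**What to change.** Keep N = 100 and rewrite the Sample size paragraph.

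1. Express the target, the SD and the rates in one unit, events per patient-year.
2. State the difference actually used and the n that it gives. If 40 already contains a dropout allowance, say so. The sponsor must supply this difference; it should not be derived from 40.
3. Reconcile that difference with the quoted 1.17 and 0.68 per year, and state the control rate expected under the entry criteria.
4. Report the power of 40 to 50 per group over a range of differences. With 40 evaluable per group and SD 1.25, it is about 95% at 1 per year and 90% at 0.91 per year, the latter given as the detectable difference and not as a new target. At 0.49 per year it is about 42% to 62%, depending on the model and the evaluable n.
5. Extend the Discussion's limitation on sample size from lung function to the primary outcome.

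The cost is one rewritten paragraph and one added sentence. No further patients are needed, and allocation, endpoint and follow-up are unchanged. The stated power becomes less favourable at the smaller differences.
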